#### Surveys

Guided by the logic model, three survey instruments have been developed to identify inputs, implementer characteristics, inner setting, and process that may be associated with each practice’s readiness to change. The first instrument, Practice Characteristics Survey, collects practice demographic information as well as responses to validated questions from the Change Process Capacility Questionnaire (CPCQ) and National Ambulatory Medical Care Survey (NAMCS). The 32-item CPCQ assesses outputs by measuring three componenets of change capacity [38, 39]. The 25-item NAMCS assesses the degree of EHR adoption and functionalities at each practice (Additional file 1). To assess external factors and the environment, we document the county in which the practice is located and if the county has a CHIO to facilitate QI and if the practice is a member of a current or previous QI network. Additionally we use the “5Ps Microsystem Dashboard” developed by Dartmouth Institute for Health Policy and Clinical Practice to describe the practice. This survey is completed by practice leadership/management.

The second instrument, the Practice Members Survey, assesses perceptions of the change process and context among clinicians and staff using the 23-item Adapative Reserve questionnaire. Adaptive Reserve includes items that demonstrate a practice's ability to make and sustain change, such as practice relationship infrastructure, alignment of management functions in which clinical care, practice operations, and financial functions share and reflect a consistent vision, leadership, teamwork, work environment, and culture of learning [40]. This survey is completed by multiple members of the same practice who occupy the clinical/administrative hierarchy (Additional file 2).

The third instrument, Electronic Practice Record, assesses utility of implementation support strategy. PFs and ADs contribute their notes to structured and semi-structured items during facilitation and academic detailing sessions for each of ABCS metrics.

#### Data sources

The H2O master dataset will include both primary and secondary data sources. The aforementioned surveys will be compiled to include variables describing organizational contexts and outputs. These data are collected by PFs during visits to practices at three time points: (1) baseline, (2) at the end of the implementation of support strategy, and (3) 6 months post-implementation. Secondary data on performance (e.g., ABCS) and patient-oriented outcomes (e.g., hospitalization, length of stay) is extracted from the EHRs and the HIE. Practice performance, i.e., the number of patients who achieved and provider performance on these measures, will be calculated for each practice (Table 2).

**Table 2 Tab2:** Outcome measures from HIE and/or EHR data

Measure (Source)	Numerator	Denominator*	Exclusion	Data Source
Aspirin (PQRS 204/NQF 0068)	Patients in denominator with documented use of aspirin or other antithrombotic	Patients 18+ years of age with Ischemic Vascular Disease diagnosis, or hospital discharge for acute myocardial infarction, coronary artery bypass graft, or percutaneous coronary interventions	On another anticoagulant, GI bleeding history, aspirin allergy	Health Information Exchange (HIE)
Blood Pressure Management 1 (PQRS 236/NQF 0018)	Patients in denominator whose blood pressure was adequately controlled (< 140/90)	Patients aged 18 through 85 years with a diagnosis of hypertension	End stage renal disease, dialysis, renal transplant, or diagnosis of pregnancy	HIE
Blood Pressure Management 2	Patients in denominator whose blood pressure was adequately controlled (age 18–59 and/or people with diabetes or chronic kidney disease < 140/90; age 60–85 < 150/90)	Patients aged 18 through 85 with a diagnosis of hypertension	Lacking a DM or CKD diagnosis	HIE
Cholesterol Management 1 (PQRS 316)	Patients in the denominator whose risk-stratified fasting LDL is at or below the recommended LDL goal	Patients aged 20 through 79 years of age who had a fasting LDL performed		HIE and chart audits
Cholesterol Management 2	Patients in the denominator who were prescribed the recommended dose of statin based on risk status	Patients aged 20 through 79 years of age who had a fasting LDL performed		HIE and chart audits
Smoking Cessation Support (PQRS 226/NQF 0028)	Patients in denominator who were screened about tobacco use one or more times within 24 months AND who received tobacco cessation counseling intervention if identified as a tobacco user	Patients age 18+ years	Documentation of medical reason(s) for not screening for tobacco use	HIE

^*^Note: Population denominators will be based on active patient—defined as patients who have been seen in the practice within the previous 18 months

*Abbreviations*: *CABG* coronary artery bypass grafting, *CKD* chronic kidney disease, *COPD* chronic obstructive pulmonary disease, *CVA* cerebral vascular accident, *DM* diabetes mellitus, *ED* emergency department, *GI* gastric intestinal, *LDL* low-density lipoprotein, *LOS* length of stay, *MI* myocardial infarction, *PQRS* physician quality reporting system, *NQF* National Quality Forum

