#### Evaluation design

A stepped-wedge cluster randomized trial design was used to evaluate the program. ABCS outcomes would be evaluated every 3 months beginning in month 7 of the project following an initial 6-month period for recruitment of the practices and practice units within each county, validation of the HIE data, and development of computing code for data abstraction from the HIE system. ABCS performance will be evaluated at each of the 263 practices during each 3-month period where the time of initiation of implementation support is randomly assigned. Each of 20 PFs were assigned to geographic sub-regions, nested within the five geographic sectors, in the state. The sub-regions reflected collections of counties that were feasible to access by a given PF. Within each sub-region, the consenting practices were randomly assigned to begin the intervention program in Wave 1, 2, 3, or 4 (Fig. 4). The targeted randomization was a total of 13 randomized practices per PF with three to four practices initiating the intervention program per Wave per PF. Random assignments were made in a manner to ensure a balance of Wave assignments for each PF and sub-region. In addition, during the 12-month implementation support period, two of the four programs were introduced in each 6-month period, where blood pressure management and smoking cessation support were introduced together and aspirin use and cholesterol management were introduced together. Within each of the four Waves, half of the counties introduced blood pressure management and smoking cessation support first and the other half introduced aspirin use and cholesterol management first, where the order assignment was randomly determined to ensure a balance by PF sub-region. The randomization sequences were generated using random number generation in Excel.

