The effect of the implementation support strategy on the mean capacity to change score (priority for improvement, change capacity, and care process content), or the log odds of dichotomous indicators of change, will be estimated using GEE to fit linear and logistic regression models, respectively, based on a within-cluster and between-cluster analysis [42]. As discussed by Hussey and Hughes [42], GEE has several attractive properties that are relevant to the analysis of data arising from stepped wedge designs, including accommodating generalized linear models that are appropriate for continuous, count and dichotomous outcome measures, as well as robustness to variance and covariance misspecification. The small sample limitations of GEE-based estimation will not be of concern in this study given that 263 practices will serve as the unit of randomization and 11 time points will be utilized in the design. The outcome variable will be a continuous score measure or a Yes/No indicator variable measures at a practice unit level. The exposure of interest will be a dummy variable indicating the implementation support strategy exposure, which will be coded according to the randomized assignment (intent-to-treat analysis). Practice unit-level data will be analyzed where the nested clustering of practice units nested within practices, nested within sub-regions will be accounted for using a structured working correlation structure [44]. Cluster sizes, by county, will vary due to the targeted sampling of metro counties (25 practices per county) and more rural counties (one to five practices per county) and therefore, a jackknife estimate of the variance will be used to maintain the size of the test [42]. The time since the initiation of the implementation support strategy will also be considered as an independent factor in the regression model, along with a time by implementation support strategy interaction, to investigate the effect of the implementation support strategy relative to the time since initiation (i.e., delayed treatment effect). If a significant time by implementation support strategy effect is found, the analyses will be stratified by time period to estimate the time-specific implementation support strategy effect. Time-varying secular trends will be considered in the model, including the implementation of other health intervention programs in the studied sub-regions. Geographic region will also be considered as a modifying factor where region is fit as a series of four indicator variables (indicator for each quadrant, with the combined Tulsa and Oklahoma City metro areas serving as the reference group). If appropriate based on estimates, a dichotomous region variable indicating metro versus non-metro locations will be considered. A Type III Wald statistic will be used to determine the overall significance of the interaction between implementation support strategy and the five degrees of freedom categorical class variable for region. A 2-sided 0.05 alpha level will be used to define statistical significance. An intention-to-treat paradigm will be followed where data from all practice units are analyzed according to the randomized assignment regardless of adherence or implementation quality.

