## Discussion

### Impact

Oklahoma is among the poorest states in the nation, with a population of 3.85 million, 75.5% of which is white, 7.6% black, 9.0% American Indian, 1.9% Asian, and 9.3% Hispanic [46]. The state has 38 federally recognized American Indian tribes and the majority of its counties are rural. Most rural communities have a large proportion of vulnerable and underserved patients. Relevant to the CVD management goals of H2O, 23.3% of Oklahomans are current smokers, 35.5% have hypertension, 31.1% are physically inactive, and 32.2% are obese [47]. In a 2011 government report, the quality of health care in Oklahoma was rated as “weak,” particularly in chronic disease management [48]. The H2O study, leveraging the establishment of OPHIC, puts forth a coordinated and systematic effort to engage and provide QI resources to practices, in both rural and urban counties, that serve vulnerable populations. Moreover, one of the reasons accounting for poor QI is the lack of infrastructure and appropriate technology. H2O provides technical and financial assistance to help practices with EHR support and connection to a HIE.

Over the course of the study, PFs, ADs, and PFCs support practices assisting them in establishing QI processes, empaneling and risk stratifying their patients, and providing care coordination for those at the highest CVD risk. Such planned care has been demonstrated to reduce hospitalizations, ED visits, utilization, and use of specialists when more active primary care is provided. In addition, practices may have the opportunity to connect to the preventive services registry or implement enhanced referral systems, both available through the HIE. All of these strategies will likely remain with the practice after study completion.

Enrollment in H2O also positions practices to new payment opportunities with OPHIC’s potential capability to negotiate purchasing of advanced primary care services. Of the 263 practices, 195 will have 12 or more months at the end of the study period to implement these advanced primary care services and be prepared for a shared savings payment plan similar to that tested in the multi-payer Comprehensive Primary Care program, or to participate in an Accountable Care Organization.

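### Three practice-timed surveys cannot by themselves support the stepped-wedge analysis planned for the capacity-to-change score; without overlap in the wave calendar it is a before-after contrast

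*Protocol article*

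**What the plan says.** **Instrument.** Under Surveys, the capacity score comes from a questionnaire within the Practice Characteristics Survey: "The 32-item CPCQ assesses outputs by measuring three componenets of change capacity".

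**Schedule.** Under Data sources, the survey data are "collected by PFs during visits to practices at three time points: (1) baseline, (2) at the end of the implementation of support strategy", with the third survey 6 months after that. These times are relative to each practice. They are not calendar dates shared across waves.

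**Roll-out.** Under Evaluation design, practices were "randomly assigned to begin the intervention program in Wave 1, 2, 3, or 4". The length of support follows from the same section: "during the 12-month implementation support period, two of the four programs were introduced in each 6-month period". Measurement every 3 months from project month 7 is stated there for the ABCS outcomes only.

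**Analysis.** Under Analytic plan, the effect on the mean capacity score is estimated by GEE "based on a within-cluster and between-cluster analysis". Exposure is a dummy variable coded by randomized assignment and described as intention-to-treat. Small-sample concerns about GEE are set aside because "263 practices will serve as the unit of randomization and 11 time points will be utilized in the design". Secular trends are to be considered, but their form is not fixed.

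**The concern.** A between-cluster contrast in a stepped wedge needs some practices already exposed while others, measured at about the same calendar time, are not. Here the first exposed capacity survey comes only when a practice has finished 12 months of support. If the last wave has given its baseline by then, no unexposed practice is left to compare with, and exposure is determined by calendar time.

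Capacity to change is the first item of the first analytic goal, and the logic model makes the outputs candidate mediators. The risk is that a change over time, including the effect of other health programmes that the Analytic plan itself anticipates, is reported as a randomized intention-to-treat effect.

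**Working it through.** **Inputs from the article:** four waves; 12 months of support; surveys at baseline, end of support and 6 months after; 263 practices recruited, at least 234 expected to be retained.

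**Assumptions:** wave spacing s (Fig. 4 is not shown; 1 to 6 months tried); lead time b from the first quarterly point to wave 1 (0 or 3 months); score SD 1; within-practice correlation 0.5 (0.3 and 0.7 also tried). The article states no power for capacity; Table 3 covers ABCS only.

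**1. The stated 11 time points.** Count months from the first quarterly point. Wave w starts at b + s(w − 1). With b = 3 and s = 3, the last survey is at 3 + 9 + 18 = 30, and 30/3 + 1 = 11. All surveys then lie within 6 + 30 = 36 project months. So 3-month spacing reproduces the figure.

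It is not the only layout that does. With s = 6 and b = 0, the last support period ends at 18 + 12 = 30, also 11 points, but the last wave's 6-month survey (month 36) falls outside the grid.

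**2. When surveys overlap.** With baselines at wave start, the last unexposed survey is at b + 3s and the first exposed one at b + 12. Concurrency needs 3s ≥ 12, so s ≥ 4.

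| Spacing (b = 3) | Unexposed surveys | End of support | 6 months after | Overlap |
|---|---|---|---|---|
| 3 months | 3, 6, 9, 12 | 15, 18, 21, 24 | 21, 24, 27, 30 | none (3-month gap) |
| 4 months | 3, 7, 11, 15 | 15, 19, 23, 27 | 21, 25, 29, 33 | month 15 only |
| 6 months | 3, 9, 15, 21 | 15, 21, 27, 33 | 21, 27, 33, 39 | months 15 and 21 |

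If all baselines are taken at enrolment before roll-out, every unexposed survey precedes every exposed one whatever the spacing.

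**3. Estimability with categorical calendar periods** (columns = intercept + exposure + distinct survey months − 1).
- 3 months, wave-start baselines: 10 months, 11 columns, rank 10. Not estimable.
- 3 months, enrolment baselines: 7 months, 8 columns, rank 7. Not estimable.
- 6 months, enrolment baselines: 6 months, 7 columns, rank 6. Not estimable.
- 6 months, wave-start baselines: 7 months, 8 columns, rank 8. Estimable, SE 0.114 SD.

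**4. Precision at 3 months, wave-start baselines.** With no trend term, the SE of the mean of two exposed scores minus baseline is √[(1 − 0.5)(1 + 1/2)/263] = 0.053 SD. With a linear trend it is 0.138 SD, a ratio of 0.138/0.053 = 2.6. Over correlations 0.3 to 0.7 the two SEs run from 0.063 to 0.041 and from 0.149 to 0.115.

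**5. What drift does to an unadjusted contrast.** Baseline versus end of support spans 12 months. With 234 practices, SE = √[2(1 − 0.5)/234] = 0.065. The rejection probability under no true effect is Φ(d/SE − 1.96) + Φ(−d/SE − 1.96).

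| Assumed drift d per year | d/SE | Rejections at nominal 5% |
|---|---|---|
| 0.05 SD | 0.76 | 12% |
| 0.10 SD | 1.53 | 33% |
| 0.20 SD | 3.06 | 86% |

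**The case against.** A reader might infer outright that exposed and unexposed surveys never overlap. The article does not support that as a fact. Wave spacing is not in the visible text, and wave-start baselines 4 or more months apart would overlap. Nor does the Impact section settle it. It says "195 will have 12 or more months at the end of the study period", and 195/263 = 74.1%, or about three waves of four. Some 3-month layouts fit this. So does a 6-month one: with starts at project months 7, 13, 19 and 25 and a 3-year evaluation counted from month 7 to month 43, the months left after support are 24, 18, 12 and 6, so three waves have at least 12. This stands, and the point must be conditional.

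A reader might also set three time points against eleven as a plain miscount. Three is the count per practice; at 3-month spacing the waves together yield 10 distinct survey months. The figure of 11 describes the design and does not say that capacity is surveyed 11 times.

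Nor does random wave assignment contribute nothing. Baselines spread over 9 months inform the trend in unexposed scores. At months 21 and 24 of the 3-month layout, end-of-support and 6-month surveys from different waves coincide, which gives a randomized comparison of time since initiation. Secular trends may be modelled. But a linear trend carries the unexposed pattern beyond the last baseline by extrapolation, and the coinciding surveys compare exposed with exposed. Neither supplies a concurrent unexposed group.

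Finally, the hypothesis and the power analysis concern ABCS, and the mediation text claims only evidence of an association. That limits the severity without removing the mismatch.

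**Conclusion.** The point holds in conditional form and is of moderate severity. Survey schedule and analysis are both stated in the article and do not fit, so this is not a detail left to a fuller plan.

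With waves under 4 months apart, or with enrolment baselines, the capacity effect is a before-after contrast. It is not estimable with calendar-period effects. With a linear trend it is estimable by extrapolation, at about 2.6 times the standard error (3-month spacing, wave-start baselines, assumed correlation 0.5). With waves 4 or more months apart and baselines at wave start, some overlap exists, and the period-adjusted contrast rests only on the overlapping months. Three-month spacing is the most natural fit to the quarterly design but remains an inference. The drift rates used are illustrative assumptions.

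The quarterly ABCS and patient-event analyses are not affected.

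**What to change.** Reconcile Data sources with the Analytic plan. State the wave calendar and whether baseline means enrolment or wave start.

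Unless that calendar gives overlap, for the capacity outcome:
- describe the analysis as pre-post change across the three surveys, with practice-clustered standard errors;
- state the trend assumption on which any adjusted estimate depends;
- drop the between-cluster, 11-time-point and randomized-effect wording;
- label any mediation analysis that uses these scores in the same way.

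If the calendar does give overlap, say which months carry the contrast.

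The cost is wording and a weaker claim for capacity. If a randomized contrast is wanted and fieldwork still allows it, wave 1 could complete the same questionnaire in the month of wave 4's baseline. At 3-month spacing that compares 3 × 3 = 9 months of support with none, for one extra short survey in one wave.

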While ABCS guidelines are well defined, adherence in the clinical setting is less than optimal. National data from the *Million Hearts Initiative* suggests that 54% of individuals at increased risk of CVD events are taking aspirin, 53% of those with hypertension have adequately controlled blood pressure, 32% of individuals with high cholesterol are effectively managed, and 22% of people trying to quit smoking get counseling or treatment [6]. Furthermore, a large number of US adults are unaware of their high blood pressure and high cholesterol. Based on data from the 2003–2010 National Health and Nutrition Examination Survey, investigators estimated that among the 66.9 million US adults aged 18 years and older with hypertension, 14.1 million (39%) are not aware of their hypertension, 5.7 million (16%) are aware of their hypertension but are not receiving pharmacologic treatment, and 16.0 million (45%) are aware of their hypertension and are being treated with medication [7]. Similarly, a large percentage of adults are unaware of their high cholesterol status, at approximately 40%, and this rate is nearly 50% among Hispanic adults [8, 9]. While risk factor reduction, focused on ABCS measures, is recognized as a valuable approach to reducing CVD deaths, adherence to ABCS screening and treatment guidelines in primary care is deficient, with high percentages of patients unaware of their elevated risk status and clinicians juggling competing demands and prioritizing more acute illness over preventive screenings. New strategies to engage patients in and provide resources to practices for ABCS screening and management are urgently needed to address these challenges.

The Healthy Hearts for Oklahoma (H2O) Study, one of the seven collaboratives funded by the Agency for Healthcare Research and Quality (AHRQ) EvidenceNOW Initiative, proposes to build a quality improvement (QI) infrastructure in the state by (1) constructing a sustainable Primary Healthcare Improvement Center (OPHIC) that serves as a resource to support dissemination and implementation (D&I) of QI methods in Oklahoma; (2) facilitating the implementation of a bundled QI intervention in primary care practices to improve the management of patients at risk for CVD events. Parallel to infrastructure building, H2O aims to conduct a comprehensive evaluation of the bundled QI intervention implementation in primary care and hypothesizes that the QI intervention is associated with improvement in ABCS measures.

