#### Power analysis and effect sizes

A series of simulation studies were performed to investigate power of the planned evaluation study [41]. A logistic regression model was used to randomly generate data corresponding to the assumed percentage of patients satisfying each ABCS criterion prior to and after the implementation support period as specified in Table 3. The model was specified according to the mean model introduced by Hussey and Hughes [42] and included a random effect corresponding to practice (the unit of randomization), a fixed implementation support effect where the implementation support covariate was modeled using a fractional covariate of (0.25, 0.5, 0.75, and 1.0) for the 3, 6, 9 and 12-month post-initiation practice performance measures to account for an implementation support strategy that is not fully effective until the 12-month time point following initiation. Note that for half of the practices, the fractional covariate is delayed by an additional 6 months relative to the Series implementation scheme given that one pair of targets (blood pressure/smoking or aspirin/cholesterol) is delayed by 6 months in each practice. The model also included a random error term. The correlation among measures made on patients from the same practice was assumed to be 0.10 or less [43]. After the data were generated, Generalized Estimating Equations (GEE) methodology was used to fit a logistic regression model to test the significance of the implementation support strategy effect. The percentage of simulated data sets that resulted in a significant intervention effect was recorded as the power of the specified study design. The power analysis assumes a 2-sided 0.05 alpha level. For each ABCS endpoint, 500 simulated data sets were generated. Estimated power is summarized for each target in Table 3. The power of the implemented analyses will be higher than that from the simulation studies, given that all active patients in the targeted clinical population for a particular ABCS criterion during a 3-month period will be analyzed per practice unit.

**Table 3 Tab3:** Summary of the assumed intervention effect sizes and power

Endpoint	Patient Cohort Characteristics (defining cohort eligible for intervention)	Baseline^a^ Percentage	Post-intervention Percentage	Power
A: Aspirin (aspirin or other antithrombotic prescribed)	Aged 18 years and older with ischemic vascular disease without a contraindication to aspirin	60%	70%	> 95%

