B1: Blood Pressure Management 1 (blood pressure adequately controlled)	Aged 18–85 who had a diagnosis of hypertension	65%	70%	> 95%
B2: Blood Pressure Management 2 (blood pressure adequately controlled as per co-morbidity-adjusted targets)	Aged 18–85 who had a diagnosis of hypertension	65%	70%	> 95%
C1: Cholesterol Management 1:** (fasting LDL test AND ≤ LDL goal)	Aged 20–79	15%	25%	> 95%
C2: Cholesterol Management 2:** (fasting LDL test AND prescribed statin if indicated)	Aged 20–79	15%	25%	> 95%
S: Smoking cessation support (screening about tobacco AND received cessation counseling if tobacco user)	Aged 18 years and older	60%	70%	> 95%

^a^Estimates for the baseline percentages for aspirin use, blood pressure management, and smoking cessation support are based on Oklahoma Foundation for Medical Quality (OFMQ) primary care practice initiatives in the state of Oklahoma

^**^The C1 and C2 measures were calculated as the product of the probability of having a fasting LDL test (estimated to be 0.3) multiplied by the probability of having an LDL measure below the target (estimated to be 0.50) or being prescribed a statin if indicated (estimated to be 0.5) conditional on having a fasting LDL test

*Abbreviation*: *LDL* low-density lipoprotein

Practices drop out of QI projects when there is a significant disruption in the practice’s internal (e.g., significant clinician or staff turnover, new EHR) or external (e.g., new ownership) environment. On average, we have experienced a drop-out rate of about 5% during a 6-month initiative from previous experience. We therefore estimated a 10% drop-out rate in this 1-year project. Among the 263 recruited practices, we expect to retain at least 234 practices for the entire duration of the 3-year evaluation program.

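### The hypertension (B1, B2) denominators, and less so the aspirin one, are open groups set by recorded diagnosis, which the support itself can change, so a shift in who is counted can bias the estimated effect in either direction

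*Protocol article*

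**What the plan says.** Protocol article, Data sources, Table 2: B1 is measured in "Patients aged 18 through 85 years with a diagnosis of hypertension", and B2 uses essentially the same group. Aspirin is measured in adults with an ischemic vascular disease diagnosis or a qualifying hospital discharge. The table note limits all denominators to patients seen in the previous 18 months. No row dates the diagnosis relative to the start of support.

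Power analysis and effect sizes: "all active patients in the targeted clinical population for a particular ABCS criterion during a 3-month period will be analyzed per practice unit". The patient-level logistic model in the Analytic plan adds no further restriction.

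Table 3 gives the assumed effects: for blood pressure "Aged 18–85 who had a diagnosis of hypertension 65% 70% > 95" percent power, and for aspirin "Aged 18 years and older with ischemic vascular disease without a contraindication to aspirin 60% 70% > 95" percent power.

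On the support itself, the Resource center section says that practices are helped to capture EHR data so that the quality measures can be calculated. The HIE and HIT support section has advisors visiting practices during the intervention period to improve electronic recording and reporting of ABCS data. The Impact section adds that facilitators support practices by "assisting them in establishing QI processes, empaneling and risk stratifying their patients". The Background cites national survey figures in which "14.1 million (39%) are not aware of their hypertension".

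**The concern.** In a stepped wedge, the effect is the contrast between exposed and unexposed quarters, adjusted for calendar time. That contrast is an effect on patients only if exposure does not alter which patients are counted. Here the denominator depends on what is recorded in the EHR, and the support works on that recording. A patient with uncoded hypertension is outside the denominator before the crossover and may be inside it afterwards. Random assignment of waves does not remove this, because recording and care change at the same randomised moment.

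A null result could then hide better control among patients already known to the practice, and a positive result could come from coding patients who were already controlled. The assumed blood pressure effect is only 5 points, so modest changes in membership matter.

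**Working it through.** **Inputs from the article.** Blood pressure 65% to 70%, aspirin 60% to 70% (Table 3). "The power analysis assumes a 2-sided 0.05 alpha level". "263 practices will serve as the unit of randomization and 11 time points will be utilized in the design". Within-practice correlation 0.10 or less. Effect build-up 0.25, 0.5, 0.75, 1.0, with half of the practices delayed by 6 months for a given pair of targets. Undiagnosed hypertension: 14.1 of 66.9 million (Background).

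**Assumptions.** g = growth of the denominator relative to its original size; c = control among newly recorded patients. The article gives neither, so ranges are shown. Patients per practice and quarter are not stated and the wave spacing is in a figure not shown, so both were varied.

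**Step 1: the plan's own power.** A Hussey–Hughes calculation on practice-quarter means (263 practices, 11 time points, correlation 0.10, the article's fractional covariate) gives, for 65% to 70%:
- waves 3 months apart: 81% with 10 patients per practice-quarter, 97.6% with 20
- waves 6 months apart: 96.2% with 10, 99.9% with 20

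The stated power above 95% is attainable with about 20 or more patients per practice-quarter. It cannot be reproduced exactly without the cluster size.

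**Step 2: measured control after a change in membership.** If true control in the known group reaches 70%,

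measured control = (0.70 + g·c)/(1 + g).

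The bias is g(c − 0.70)/(1 + g): negative if c is below 70%, positive if above.
- g = 5%, c = 30%: 0.715/1.05 = 68.1% (gain 3.1 points)
- g = 10%, c = 30%: 0.730/1.10 = 66.4% (gain 1.4 points)
- g = 10%, c = 0: 0.700/1.10 = 63.6% (loss 1.4 points)
- g = 10%, c = 80%: 0.780/1.10 = 70.9% (gain 5.9 points)

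If true control stayed at 65%, g = 10% and c = 80% would still give (0.65 + 0.08)/1.10 = 66.4%, an apparent gain of 1.4 points with no change in care.

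**Step 3: growth that cancels the assumed gain.** Setting measured control back to baseline gives g = 0.05/(0.65 − c) for blood pressure and g = 0.10/(0.60 − c) for aspirin.

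| c | Blood pressure (5 points) | Aspirin (10 points) |
|---|---|---|
| 0 | 7.7% | 16.7% |
| 20% | 11.1% | 25% |
| 30% | 14.3% | 33% |
| 40% | 20% | 50% |
| 50% | 33% | 100% |

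**Step 4: is such growth possible?** From the counts, 14.1/(66.9 − 14.1) = 26.7% of those aware. (The printed 39% fits a base of 14.1 + 5.7 + 16.0 = 35.8 million, not 66.9 million, so the counts are used.) Cancelling the blood pressure gain means recording 29%, 42%, 54%, 75% or 125% of that pool at c = 0, 20%, 30%, 40% or 50%. At c = 50% the pool alone cannot do it. The article gives no such pool for ischemic vascular disease.

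**Step 5: effect on power.** With 20 patients per practice-quarter and c = 30%, power falls from 97.6–99.9% to 68–89% at 5% growth and 19–29% at 10% growth. The ranges span the two wave spacings.

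**The case against.** A reader might infer that the programme finds hidden hypertension and vascular disease, so that success necessarily lowers measured control and wipes out the gain for both measures. The article does not support this. The list of intervention components contains no case-finding. The call for screening is motivation in the Background, and risk stratification appears in the Discussion, tied to care coordination. Help with recording is documented; help with finding is inference. Documentation support could equally add treated patients who were never coded, which raises the measure. New patients would also be treated under the same support, so their control may rise. The 5-point gain belongs to blood pressure alone. Aspirin assumes 10 points, and its entry by hospital discharge depends less on practice coding. The undiagnosed pool is a national survey figure, not a count of uncoded patients on these practices' active panels.

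It can also be said that the open denominator is deliberate. Table 2 ties B1 and aspirin to standard published measures, and the Logic model section names practice performance as the outcome, which is a legitimate target. The full measure specifications are not shown and might contain a timing rule for the diagnosis.

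All of this stands as a limit on the claim. It does not remove the point. The article states whom it analyses, and that group is open. Even as a performance measure, a change in the percentage cannot be credited to better control if the support also changed who is in the denominator. An unknown sign makes interpretation harder.

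**Conclusion.** The concern holds in a limited form. Membership of the B1 and B2 denominators, and to a lesser extent of the aspirin denominator, can change at the randomised crossover because the support acts on recording. The resulting bias in the estimated effect on control can go either way. For blood pressure, growth of about 8–20% would cancel the assumed 5-point gain if control among new entrants is 0–40%, whereas at 80% control 10% growth would inflate the measured figure to 70.9%. Aspirin is less exposed: 17–50% growth at 0–40%, with no figure in the article to show that such growth is available. Growth and control among new entrants are assumptions throughout. The documents show that the bias is possible and that modest shifts matter for blood pressure; they do not show that it will occur, or in which direction.

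**What to change.** Keep the open quarterly measure as the description of practice performance. Replacing it by a closed group as the main analysis is a debatable choice of target and is not needed.

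Add to the Analytic plan:
- A prespecified parallel analysis of aspirin, B1 and B2, with the same model, limited to active patients whose qualifying diagnosis or event was recorded before one common date for all waves that precedes any support. The start of measurement in month 7 is a candidate, to be checked against the Wave 1 start.
- Denominator size and number of new diagnoses per quarter, reported by exposure status.
- A rule that better control is claimed only where the open and restricted analyses agree.

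The cost is a little extra analysis and a need for dated diagnoses in the HIE/EHR extract, which the article does not confirm. The restricted group shrinks as patients cease to be active, leaves out later vascular events, and depends on how complete coding was before support, so it complements the open measure.
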